**Specific Aim 2:**

Statistical differences in serum metabolites between experimental groups will be evaluated using paired t-tests and False Discovery Rates (q-values).

**Power and Sample Size Considerations.** Our study is designed to yield 20 participants who will

complete the study. Based on the mean and SD for CRP in the 1999-2000 NHANES data restricted to our inclusion criteria (20-55y and BMI 25-30) and an intra-class correlation coefficient for CRP ranging from 0.60-0.80, we estimate 80% power to detect a 40-56% change in CRP with the probability of a type I error set at 0.05. As with any pilot study our power is limited. However information from this pilot study will be used to support a future R01 submission for a larger RCT, including information on: methods of recruitment and compliance, estimated effect size from a randomized trial and sample size needed, and new G&C pathways that may serve as additional biomarker endpoints.

**1.10. Project Timeline**

Our intention is to complete this project in 12 months; however, we have allocated up to 2 years in the event that we have a delay in recruitment of desired study participant population. During the first 2 months of the study, IRB materials will be created, data entry systems will be organized; forms will be printed. Starting in the third month, 30 participants will be recruited on a rolling-enrollment basis for participation in the intervention, with the goal of 20 completed all study activities. Liver and kidney function panels will be conducted routinely to ensure that participants can be enrolled on an ongoing basis. Biological samples from the intervention will be stored until each participant has completed both treatments so that samples for each participant can be analyzed together to minimize assay variation. Data analysis will begin, and the manuscript will be prepared during months 11 and 12.

|  | **1** | **2** | **3** | **4** | **5** | **6** | **7** | **8** | **9** | **10** | **11** | **12** |
| --- | --- | --- | --- | --- | --- | --- | --- | --- | --- | --- | --- | --- |
| Start up, Forms, IRB |  |  |  |  |  |  |  |  |  |  |  |  |
| Recruitment |  |  |  |  |  |  |  |  |  |  |  |  |
| G&C Intervention |  |  |  |  |  |  |  |  |  |  |  |  |
| Data Analysis |  |  |  |  |  |  |  |  |  |  |  |  |
| Manuscript Preparation |  |  |  |  |  |  |  |  |  |  |  |  |

**1.11. DATA SAFETY AND MONITORING PLAN**

Oversight for this study will be provided by the Principal Investigator, [name], with delegation of responsibilities to the Project Director, [name]. They will ensure all entry criteria are met prior to the initiation of the protocol, and all study procedures and reporting of adverse events are performed according to the IRB-approved protocol.

All adverse events related to the study procedures will be fully documented on the appropriate case report form(s) and entered in a study database. For each adverse event, the investigator will provide the onset, duration, intensity, treatment required, and outcome, including documentation of need for premature termination of any study procedures.

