**Anticipated adverse events related to this study are:**

**Glucosamine and Chondroitin (G&C):** G&C are among the most commonly used supplements in the U.S. In large human intervention trials, only mild symptoms, e.g., stomach upset, have been reported. The potential for unexpected adverse experiences to G&C are minimal. Participants will keep a daily study log which will include questions on health status and possible adverse experiences. Study staff will contact study participants at least bi-weekly while they are in a treatment period (including placebo) by phone (or email if the participant so requests) to ask about possible adverse experiences, assess compliance and address any questions or problems the participant may be having. The study manager has an emergency cell phone and can be reached 24/7 by study participants. The phone number will appear prominently on all study materials including the daily diary.

**Blood Draws:** Participants may experience a little discomfort or have a temporary bruise from having blood drawn. Occasionally a participant may feel lightheaded or feel faint when having blood drawn. Blood will be taken only by trained personnel using established procedures. The participants will be sitting down when the blood is drawn. If a participant feels faint, they will be instructed to lie down until the feeling goes away.

Adverse event grading scale:

**0= No Adverse Event** or within normal limits

**1= Mild Severity:** Transient laboratory test alterations; discomforts noted but no disruption of daily activities; no therapy, or only symptomatic therapy required
**2= Moderate Severity:** Laboratory test alterations indicating injury without long-term risk; discomfort sufficient to modify normal daily activity; specific therapy required (i.e., more than symptomatic)
**3= Serious Severity:** Laboratory test indicating a serious health threat or permanent injury; incapacity, inability to work, inability to perform normal daily activity; hospitalization required or prolonged; emergency treatment required; life-threatening events; death

**Plan for unanticipated AE reporting:** All unanticipated AEs related to the study procedures that are severe or serious will be reported by Drs. [name] or [name] to the IRB within 7 days of notification of the investigator

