**Plan for anticipated AE reporting**: All serious anticipated AEs related to the study procedures will be reported by Drs. [name] or [name] to the IRB within 7 days of notification of the investigator

**Plan for ongoing review of results:** The PI will be notified within 24 hours by the research manager of any early terminations due to an adverse event

**Plan for safety review:** the PI will perform a cumulative review of all adverse events and premature terminations review every 6 months after study initiation or after completion of 50% of participant visits, whichever occurs first

**Plan for annual reporting:** A summary of the investigation including all adverse events and how they were handled, enrollment, drop-outs and reason for discontinuation and any protocol modifications will be provided to the IRB on an annual basis

Final Report will contain:

1. The number of adverse events and an explanation of how each event was handled
2. The number of complaints and how each complaint was handled
3. The number of subject withdrawals and an explanation of why the subject withdrew or was withdrawn
4. The number of protocol deviations and how each was handled

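### Database entry is required only for adverse events related to study procedures, yet the safety review and reports are to cover all adverse events

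*Protocol*

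**What the plan says.** All of the relevant text is in protocol section 1.11, Data Safety and Monitoring Plan.

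- **Documentation.** The opening part says: "All adverse events related to the study procedures will be fully documented on the appropriate case report form(s", and the same sentence sends those events to the study database. The next sentence lists what is recorded: "For each adverse event, the investigator will provide the onset, duration, intensity, treatment required, and outcome", together with any need to stop a study procedure early. Relatedness is not in that list.
- **Collection from participants.** Under the heading on anticipated adverse events: "Participants will keep a daily study log which will include questions on health status and possible adverse experiences". Also: "Study staff will contact study participants at least bi-weekly while they are in a treatment period (including placebo) by phone", or by email on request. These contacts ask about possible adverse experiences, among other things. Neither source is limited by relatedness.
- **Expedited reporting to the IRB.** "All unanticipated AEs related to the study procedures that are severe or serious will be reported" within 7 days. The parallel rule for anticipated events covers serious ones, again only those related to study procedures.
- **Review and reports.** Under the plan for safety review, "the PI will perform a cumulative review of all adverse events and premature terminations", at 6-month intervals or once half of the participant visits are complete, whichever comes first. The annual report to the IRB is likewise to summarize all adverse events and their handling. The final report is to give the number of adverse events and how each was handled. None of these three carries a relatedness limit.

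**The concern.** The step that turns a reported symptom into a database record has a narrower scope than the outputs that follow it. If the database is the source for the principal investigator's review and for the IRB reports, then a review of all adverse events becomes a review of those someone considered related.

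The filter is also undefined. Nobody is assigned to judge relatedness, no criteria are given, and the judgement is not recorded. Two staff members could take different events from the same log, and nobody could later reconstruct which were left out or why. Section 1.11 itself expects little potential for unexpected reactions to G&C. Under that expectation an unfamiliar symptom is easily put down to another cause, and that is the kind of event a cumulative review should be able to see.

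At stake is the completeness of safety monitoring and of the reports to the IRB.

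**Working it through.** No arithmetic decides this point, and the plan states no figure to reproduce. The check follows an adverse event through section 1.11 and compares the scope at each step.

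| Step | Where in section 1.11 | Scope as written |
| --- | --- | --- |
| Daily log | Anticipated adverse events, G&C paragraph | Possible adverse experiences, no relatedness limit |
| Staff contact | Same paragraph | Same, in G&C and placebo periods alike |
| Case report form and database | Opening part | Events related to study procedures |
| Expedited report, unanticipated | Plan for unanticipated AE reporting | Related, and severe or serious |
| Expedited report, anticipated | Plan for anticipated AE reporting | Related, and serious |
| Cumulative review | Plan for safety review | All adverse events |
| Annual summary | Plan for annual reporting | All adverse events |
| Final count | Final Report list | Adverse events, no relatedness limit |

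1. Scope is wide at collection, narrow at documentation, and wide again at review and reporting. The expedited rules are narrow too, but they do not conflict with the rest: a subset for rapid reporting can be drawn from a complete record. A complete review cannot be drawn from a record that need hold only a subset.

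2. Take an event that is in the log, is mentioned at a staff contact, and is considered unrelated. The documentation sentence does not require it to be entered. The safety review, annual summary and final count all require it to be included. The protocol describes no other route by which it would reach them.

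3. Could the filter be applied consistently as written? It needs a judge, a criterion and a record of the decision, and section 1.11 supplies none of them. The expedited rules also turn on relatedness, so the plan depends on that judgement in three places without recording it.

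4. Does any planned analysis depend on the missing events? The aims in section 1.3 are serum hsCRP and serum metabolomic patterns, and section 1.9.c gives tests for those two only. No planned analysis depends on them.

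5. How large could the gap be? It equals the number of reported events considered unrelated and not entered. The document gives neither an expected number of events nor a proportion judged unrelated, so no range can be derived. The amount of source material does have a ceiling: 30 participants × 2 periods × 28 days = 1,680 treatment days. For the 20 expected completers it is 20 × 2 × 28 = 1,120.

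**The case against.** The strongest reply is that section 1.11 intends all adverse events and contains one loosely worded sentence. That sentence guarantees full documentation for related events and does not say that others go unrecorded. The following sentence speaks of each adverse event without qualification, and the review and report paragraphs speak of all of them. This is a fair reading of the likely intent. It does not remove the conflict. The following sentence can equally mean each event so documented, and the relatedness phrase recurs in both expedited rules, so it may be deliberate. Staff who follow the text as written would still be free to leave unrelated events out.

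A reader might infer that unrelated events are lost altogether. The documents do not support that. The log and the contacts gather possible adverse experiences unfiltered in both treatment periods. Early terminations due to an adverse event go to the principal investigator within 24 hours, and withdrawals are reported with reasons. The gap lies between those sources and the database. Nor does the protocol say that the database is the only source for the reviews.

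A reader might also infer that the wording spoils a safety comparison of G&C with placebo. No such comparison is planned, and none of the items that section 1.9.c hopes to carry to a larger trial is a safety rate. That part of the objection stands in full.

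Finally, one might read the reference to procedures as excluding effects of the supplement. The heading "Anticipated adverse events related to this study are" covers G&C as well as blood draws, so supplement effects appear to be included. The opening sentence would still be clearer if it said so.

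**Conclusion.** The point holds as a conflict of scope within section 1.11. Required documentation covers events related to study procedures, while the promised review and reports cover all adverse events, and the relatedness judgement that separates the two is neither assigned nor recorded. Followed as written, the documentation rule need not supply what the review and reports promise, so they may rest on an incomplete set selected by attribution.

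The consequence assumes that the reviews draw mainly on the database and that staff apply the sentence literally. If the principal investigator also reads the logs and contact notes, the practical gap shrinks, but the text does not provide for that. The number of events affected cannot be estimated from the protocol. The hsCRP and metabolomic analyses are untouched, and no effect on a treatment comparison of safety is claimed.

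This is not something a statistical analysis plan could settle. What is entered on the case report form is a collection rule that the protocol fixes, and events never entered cannot be tabulated later. It is a modest point, worth making because the repair is cheap.

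**What to change.** Reconcile the passages in section 1.11 by removing the relatedness limit from the documentation sentence, so that every adverse event arising from the daily logs or staff contacts is entered on the case report form and in the database. Add two items to the list recorded per event: the treatment period in which it occurred, and its relatedness, with the role responsible for that judgement named.

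Leave the expedited IRB reporting criteria unchanged. They would then select from a complete record, using a relatedness judgement that is on file.

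The cost is slightly more data entry, for at most 30 participants over two 28-day periods, from information that the logs and contacts already collect. No extra visit, sample or participant contact is needed.

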**Anticipated adverse events related to this study are:**

**Glucosamine and Chondroitin (G&C):** G&C are among the most commonly used supplements in the U.S. In large human intervention trials, only mild symptoms, e.g., stomach upset, have been reported. The potential for unexpected adverse experiences to G&C are minimal. Participants will keep a daily study log which will include questions on health status and possible adverse experiences. Study staff will contact study participants at least bi-weekly while they are in a treatment period (including placebo) by phone (or email if the participant so requests) to ask about possible adverse experiences, assess compliance and address any questions or problems the participant may be having. The study manager has an emergency cell phone and can be reached 24/7 by study participants. The phone number will appear prominently on all study materials including the daily diary.

**Blood Draws:** Participants may experience a little discomfort or have a temporary bruise from having blood drawn. Occasionally a participant may feel lightheaded or feel faint when having blood drawn. Blood will be taken only by trained personnel using established procedures. The participants will be sitting down when the blood is drawn. If a participant feels faint, they will be instructed to lie down until the feeling goes away.

Adverse event grading scale:

**0= No Adverse Event** or within normal limits

**1= Mild Severity:** Transient laboratory test alterations; discomforts noted but no disruption of daily activities; no therapy, or only symptomatic therapy required
**2= Moderate Severity:** Laboratory test alterations indicating injury without long-term risk; discomfort sufficient to modify normal daily activity; specific therapy required (i.e., more than symptomatic)
**3= Serious Severity:** Laboratory test indicating a serious health threat or permanent injury; incapacity, inability to work, inability to perform normal daily activity; hospitalization required or prolonged; emergency treatment required; life-threatening events; death

**Plan for unanticipated AE reporting:** All unanticipated AEs related to the study procedures that are severe or serious will be reported by Drs. [name] or [name] to the IRB within 7 days of notification of the investigator

**Plan for anticipated AE reporting**: All serious anticipated AEs related to the study procedures will be reported by Drs. [name] or [name] to the IRB within 7 days of notification of the investigator

**Plan for ongoing review of results:** The PI will be notified within 24 hours by the research manager of any early terminations due to an adverse event

**Plan for safety review:** the PI will perform a cumulative review of all adverse events and premature terminations review every 6 months after study initiation or after completion of 50% of participant visits, whichever occurs first

**Plan for annual reporting:** A summary of the investigation including all adverse events and how they were handled, enrollment, drop-outs and reason for discontinuation and any protocol modifications will be provided to the IRB on an annual basis

Final Report will contain:

1. The number of adverse events and an explanation of how each event was handled
2. The number of complaints and how each complaint was handled
3. The number of subject withdrawals and an explanation of why the subject withdrew or was withdrawn
4. The number of protocol deviations and how each was handled

